##### **Safety**

|                                                                          |                                                                                                                                                                                                                                                                                                                                                                                                                                                                                              |
|--------------------------------------------------------------------------|----------------------------------------------------------------------------------------------------------------------------------------------------------------------------------------------------------------------------------------------------------------------------------------------------------------------------------------------------------------------------------------------------------------------------------------------------------------------------------------------|
| Congestive heart failure                                                 | 
 
Pre-tibial edema rise of <math>\geq</math> 2 (grade 1-4), measured at triage, after 3h, 24h and 48h
 
PoCUS congestion assessment, after 3h, and 24h (e.g. IVC <math>></math>2 cm and collapse <math><</math>50%; wet lung <math>\geq</math> 3 B lines in any given region)
 
Loop diuretic use within 7 days, determined daily
 
Decompensated heart failure within 7 days, based on the physicians' judgement
 
 |
| Respiratory insufficiency and acute respiratory distress syndrome (ARDS) | Any of the following within 7 days: 
 
PaO2/FiO2* <math><</math> 53 kPa
 
(Non-)invasive mechanical ventilation or ECMO
 
                                                                                                                                                                                                                                                                                       |

|                                    |                                                                                                                                                                                                                                                                                                                                                                                                                                                                                                  |
|------------------------------------|--------------------------------------------------------------------------------------------------------------------------------------------------------------------------------------------------------------------------------------------------------------------------------------------------------------------------------------------------------------------------------------------------------------------------------------------------------------------------------------------------|
| Acute kidney injury                | 
 
• AKI based on KDIGO criteria within 48 hours
 
• AKI based on KDIGO criteria within 7 days
 
• Change in Serum Creatinine Levels from Baseline to 48 hours
 
• Change in Serum Creatinine Levels from Baseline to day 7 (or hospital discharge, whichever came first)
 
• Requirement for renal replacement therapy (RRT) within 7 days
 
• Requirement for renal replacement therapy (RRT) within 30 days
 
 |
| Major Adverse Cardiac Event (MACE) | Any of the following within 30 days: 
 
• Cardiovascular death
 
• Nonfatal myocardial infarction
 
• Nonfatal stroke
 
                                                                                                                                                                                                                                                                                                               |
| Vasopressor therapy                | 
 
• Vasopressor therapy within three hours
 
• Vasopressor therapy within 7 days
 
• Time to vasopressor therapy
 
                                                                                                                                                                                                                                                                                                                   |
| All-cause mortality                | 
 
• Mortality within 48 hours
 
• In-hospital mortality
 
• Mortality within 30 days
 
                                                                                                                                                                                                                                                                                                                                               |

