### 4.2 Inclusion criteria

In order to be eligible to participate in this study, a subject must meet all of the following criteria:

- Adult patients ( $\geq 18$  years of age);
- Referred to internal medicine, nephrology, geriatric medicine, oncology, hematology, lung medicine, rheumatology, gastrointestinal / liver medicine, urology, or emergency medicine (non-trauma);
- Confirmed or suspected infection according to the physician's judgement upon arrival to the ED, based the presence of an acute phase response not due to an alternative non-infectious cause (i.e., body temperature  $< 36^{\circ}\text{C}$  or  $> 38^{\circ}\text{C}$ , leukocyte count  $> 12 \times 10^9/\text{L}$  or C-reactive protein  $> 50 \text{ mg/L}$ ), and/or on symptoms suggestive for an infection (e.g. productive cough, dyspnea, dysuria, pollakisuria, abdominal pain, erythema)
- Need for hemodynamic resuscitation, based on any of the following (*first measurement at ED arrival [triage]*):
  - Mean arterial pressure (MAP)  $< 70 \text{ mmHg}$
  - Systolic blood pressure (SBP)  $< 90 \text{ mmHg}$  or a SBP decrease  $> 40 \text{ mmHg}$
  - Lactate  $> 4.0 \text{ mmol/L}$
  - Shock index\*  $> 0.9$
- Enrolled in study within one hour after ED arrival

\* Shock index is the heart rate divided by the systolic blood pressure, an indicator for the severity of hypovolemic shock.

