#### 8.1.2 Secondary study parameters/endpoints

##### **Efficacy**

|                           |                                                                                                                                                                                                                                                                                                                                                                                               |
|---------------------------|-----------------------------------------------------------------------------------------------------------------------------------------------------------------------------------------------------------------------------------------------------------------------------------------------------------------------------------------------------------------------------------------------|
| Hospital admission        | 
 
Length-of-stay in hospital
 
ICU admission within 7 days (excluding subjects receiving protocolized vasopressor therapy)
 
                                                                                                                                                                                                             |
| New onset organ failure   | Any of the following within 48 hours: 
 
Rise in SOFA score of at least 2
 
Organ support (i.e. vasopressor use [non-]invasive mechanical ventilation, acute dialysis, ECMO)
 
                                                                                                                                                            |
| Fluid resuscitation       | 
 
Volume of IV fluid resuscitation within three hours (including prehospital fluids administered)
 
Volume of IV fluid resuscitation within 7 days
 
Fluid balance within three hours (i.e difference between volume of intravenous plus oral fluids and the volume of fluid output (i.e. urine output and other fluid losses))
 
 |

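### PoCUS congestion, loop diuretic use and the respiratory item are defined without reference to the state at arrival, which dilutes any true difference in fluid overload

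*Protocol*

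**What the plan says.** The Safety table in protocol section 8.1.2 lists, under congestive heart failure:

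- Oedema: "Pre-tibial edema rise of" at least 2 grades, "measured at triage, after 3h, 24h and 48h". This is anchored to arrival.
- Ultrasound: "PoCUS congestion assessment, after 3h, and 24h (e.g. IVC" above 2 cm with collapse below 50%, or at least 3 B lines in any one region. No arrival value enters.
- Diuretics: "Loop diuretic use within 7 days, determined daily". Home use is not set aside.
- "Decompensated heart failure within 7 days, based on the physicians' judgement". Whether a case present at arrival counts is not stated.

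The next row, "Respiratory insufficiency and acute respiratory distress syndrome (ARDS"), is met by PaO2/FiO2 below 53 kPa, ventilation or ECMO at any time within 7 days, again with no baseline condition.

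Elsewhere in 8.1.2 the plan does anchor. New-onset organ failure includes "Rise in SOFA score of at least 2", and two of the kidney items are changes in creatinine from baseline.

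On eligibility, section 4.2 admits lung medicine referrals and counts "symptoms suggestive for an infection (e.g. productive cough, dyspnea, dysuria, pollakisuria, abdominal pain, erythema") towards suspected infection. Section 4.3 excludes known advanced heart failure and a primary diagnosis of acute pulmonary oedema. It does not exclude milder heart failure or long-term diuretic use.

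**The concern.** Taken as written, a patient with pneumonia and B lines in one lung region at arrival can be recorded under congestive heart failure at 3 h. A long-term loop diuretic user counts as soon as home treatment is continued or resumed within 7 days. A patient below the PaO2/FiO2 cut-off on arrival counts as having respiratory insufficiency whatever fluid follows. None of these events can be due to the allocated strategy.

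The introduction expects guided resuscitation to limit overhydration. Section 10.4 names ultrasound assessment of fluid status and tolerance as a precaution against wrong guidance from the monitor. The plan has no DSMB (8.12) and no interim analysis (9.6), so the final between-arm comparison of such items is an important part of the evidence on fluid harm. If many of the counted events predate the first bolus, that comparison loses sensitivity to benefit and to harm.

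**Working it through.** **The plan's own figure.** The protocol gives no event rate or power for these items. Its sample size concerns the primary endpoint only, and it reproduces. The averaged SD is √((2.85² + 3.44²)/2) = 3.159 L. With a difference of 1.37 L the normal formula gives 84 per arm, and a Welch simulation with 50,000 replicates gives 80.2% power at 85 per arm. Only the 94 randomised per arm is used below.

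**Side by side (8.1.2 against Table 1 in 8.3).**

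| Item | Anchored to arrival? | Arrival data in Table 1 |
|---|---|---|
| Oedema | Yes, a rise | 0 h |
| SOFA | Yes, a rise | Triage and 0 h |
| Creatinine change | Yes | Triage |
| PoCUS congestion | No | 0 h |
| Loop diuretic use | No | Use at 0 h; dose not named |
| PaO2/FiO2 | No | Not named; would have to come from the severity scores |
| Ventilation/ECMO | No | Organ support at triage and 0 h |

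**Dilution.** Let b be the share already positive at arrival, and q the risk of new onset in the rest. If every patient positive at arrival is counted, the observed risk is b + (1 − b)q. The risk difference shrinks by the factor (1 − b), and the risk ratio moves towards 1.

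**Power.** Two-sided 5% test of two proportions with n per arm: Φ{[d − 1.96√(2p̄(1 − p̄)/n)] / √[(p₁(1 − p₁) + p₂(1 − p₂))/n]}, where d is the risk difference and p̄ the mean of the two risks. The as-written version uses n = 94. The new-onset version uses 94(1 − b) with the undiluted risks.

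Assumed new-onset risk 10% (intervention) versus 20% (control):

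| b | Observed risks | Ratio | Power as written | At risk per arm | Power, new onset |
|---|---|---|---|---|---|
| 0% | 10% vs 20% | 0.50 | 0.48 | 94 | 0.48 |
| 20% | 28% vs 36% | 0.78 | 0.22 | 75 | 0.40 |
| 40% | 46% vs 52% | 0.88 | 0.13 | 56 | 0.32 |
| 60% | 64% vs 68% | 0.94 | 0.08 | 38 | 0.23 |

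Example for b = 40%: 0.4 + 0.6 × 0.10 = 0.46 and 0.4 + 0.6 × 0.20 = 0.52; 0.46/0.52 = 0.88.

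With 15% versus 30% and b = 20%, 40% or 60%, the observed ratio is 0.73, 0.84 or 0.92. Power as written is 0.40, 0.23 or 0.14, against 0.60, 0.48 or 0.34 with a new-onset definition.

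**The 53 kPa cut-off.** On room air it means a PaO2 of 53 × 0.21 = 11.1 kPa, or about 83 mmHg. The documents do not say how many patients arrive below that.

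**The case against.** A reader might infer that findings present at arrival hide any fluid overload the treatment causes, or that they bias the comparison in favour of one arm. The protocol does not support either. Allocation is random, so such findings fall equally on both arms in expectation; the contrast shrinks but does not vanish. Nor does the point cover every congestion and respiratory measure: oedema is already a rise from triage, and decompensated heart failure rests on the physician's judgement.

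Other objections:

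- **Deferral.** Section 9.2 leaves binary and time-to-event secondary analyses to a later plan. It defers the analysis; the definitions are set in 8.1.2. A later plan could repair this, but nothing in the protocol says that it will.
- **Not a fixed rule.** The ultrasound thresholds are introduced as examples, and the line is worded as an assessment. This is fair, and it is why findings at arrival *can* count, rather than certainly do. PaO2/FiO2 carries an asterisk with no footnote in the text available, so a qualifier may have been lost.
- **Other measures exist.** Infused volume, fluid balance, oedema, SOFA and creatinine also bear on the question. This limits the importance of the point. It does not make the three items informative.
- **Power is low anyway.** At 10% versus 20% it is only 0.48 with no prevalent cases. That is true, and the trial is not sized for these items. The as-written definition still costs a good part of what power there is.
- **New onset alone loses information.** A patient already below 53 kPa who deteriorates without ventilation would drop out of a purely new-onset count. This stands, and the fix therefore includes worsening.

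**Conclusion.** The point holds for three secondary safety items: PoCUS congestion, loop diuretic use, and PaO2/FiO2 or ventilatory support. Unlike comparable outcomes in the same section, they ignore the state at arrival, in a population where that state will sometimes already be positive. The consequence is attenuation and lost power. For an assumed true ratio of 0.50 (10% versus 20%), the observed ratio is 0.78 to 0.94 over a prevalence of 20% to 60%.

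The direction holds for any non-zero prevalence. The size rests on assumed risks and prevalences that the documents do not supply, and on findings at arrival persisting to the assessment; if some clear, the dilution is smaller. The primary endpoint is unaffected. The change is worth making because most of the baseline data needed are already scheduled.

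**What to change.** In section 8.1.2:

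- **PoCUS congestion:** define it as new or worsened against the 0 h ultrasound, for example absent at 0 h and present at 3 h or 24 h, or more regions affected.
- **Loop diuretic:** define it as newly started in patients not on a loop diuretic at 0 h. Count dose increases only where dose is recorded, since Table 1 names use and not dose.
- **Respiratory item:** define it as new ventilatory support, or PaO2/FiO2 newly below the cut-off or worsened by a pre-stated amount against the arrival value where there is one. State the rule for patients with no arrival blood gas.
- **Reporting:** give the prevalence at arrival by arm, and keep the presence version as a supporting summary.

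Align Table 1 with the endpoint windows: it has no 3 h column for PoCUS, and its medication row stops at 48 h while the diuretic item runs daily to 7 days.

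The cost is mostly wording, but not only that. Fewer events will be counted. Baseline PaO2/FiO2 is not listed by name, so the missing-value rule will matter, and the Table 1 corrections make explicit some data collection that the endpoints already presuppose.

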#### 4.4 Sample size calculation

##### Estimated sample size

Sample size was calculated using R (version 4.3.1), based on data from a comparable study with similar methodology and endpoint definitions (14). That reference study demonstrated a mean difference of 1.37 L in positive fluid balance at 72 hours between groups, with the intervention group showing  $0.65 \pm 2.85$  L compared to  $2.02 \pm 3.44$  L in the control group (14). The effect size (Cohen's  $d = 0.45$ ) was calculated from the reported means and standard deviations.

We conducted an a priori power analysis via a Monte Carlo simulation (50,000 replicates) assuming normal distributions for each arm with observed means and standard deviations. To accommodate unequal variances, a two-tailed Welch's t-test ( $\alpha = 0.05$ ) was applied in the simulated dataset. The simulation showed that 170 participants (85 per group) are needed to achieve 80% power to detect a statistically significant difference in the primary endpoint (IV fluid volume administered within the first three hours after study enrollment). Anticipating 10% drop-out due to loss to follow-up, study withdrawal, or protocol deviations, the total planned sample size is 188 participants (94 per group).

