| Demographic data (i.e. age, sex, ethnicity, length, weight, BMI)                                                       |               | x               |                  |            |           |            |
| Medication use (i.e. cardiovascular, immunosuppressiva, diuretics)                                                     |               | x               | x                | x          |           |            |
| Co-morbidity (pre-existent, developing)                                                                                | x             |                 | x                | x          | x         | x          |
| Mortality (in-hospital, out-of-hospital)                                                                               |               |                 | x                | x          | x         | x          |
| Hospital admission (i.e. general ward, ICU)                                                                            |               | x               | x                | x          | x         | x          |
| Disease severity scores (i.e. SIRS, [q]SOFA, NEWS)                                                                     | x             | x               | x                | x          | x**       |            |
| Vital parameters (i.e. SBP, DBP, heart rate, respiratory rate, SpO2, temperature, GCS, CRT)                            | x             | x               | x                | x          |           |            |
| Lab values (i.e. leukocytes (including machine differential), thrombocytes, creatinin, bilirubin, CRP, albumin, ureum) | x             |                 | x                | x          | x         |            |
| Extended lab values (i.e. pH, lactate, NT-proBNP)                                                                      | x             |                 | x                |            |           |            |
| Organ support information (i.e. hemodynamic support, RRT, [non-]invasive mechanical ventilation, ECMO)                 | x             | x               | x                | x          | x         | x          |
| Volume of IV fluids (time, amount, type)                                                                               | x             | x               | x                | x          |           |            |

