### 9.2 Secondary study parameter(s)

Secondary endpoints are included in statistical analysis regardless of the outcome of the primary endpoint . Similar to the primary analysis, differences between the study groups will be analyzed using the Mann-Whitney U test for non-normally distributed data and an independent samples Student's t-test for normally distributed data. A p-value of  $<0.05$  will be considered significant.

For binary and time-to-event analyses concerning secondary study parameters, a detailed analysis plan will be developed and finalized in a timely manner.

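### The two change-in-creatinine safety endpoints are tested without adjusting for the triage creatinine already collected, which loses some precision but causes no bias

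*Protocol*

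**What the plan says.** The acute kidney injury row of the Safety table in protocol section 8.1.2 contains two continuous measures: "Change in Serum Creatinine Levels from Baseline to 48 hours" and "Change in Serum Creatinine Levels from Baseline to day 7 (or hospital discharge, whichever came first"). The other four renal items are binary: KDIGO injury by 48 hours and by 7 days, and renal replacement therapy by 7 and by 30 days.

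Section 9.2 says that group differences "will be analyzed using the Mann-Whitney U test for non-normally distributed data and an independent samples" Student's t-test for normal data. No covariate is named. The same section postpones only part of the work: "For binary and time-to-event analyses concerning secondary study parameters, a detailed analysis plan will be developed and finalized in a timely manner". The comparison of continuous secondary endpoints is therefore fixed in the protocol.

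Table 1 in section 8.3 includes creatinine in its laboratory row ("thrombocytes, creatinin, bilirubin, CRP, albumin, ureum"), marked at triage, 24 h, 48 h and 7 d.

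**The concern.** A change score subtracts the whole baseline value, whatever the correlation between baseline and follow-up. When that correlation is below 1 and the two SDs are similar, this over-corrects and leaves avoidable noise in the comparison. Regression on baseline estimates how much to subtract.

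Scale is a second issue. Section 4.3 excludes only dialysis-dependent disease or an eGFR below 15, so patients with substantially raised creatinine can enter. A 20% rise is 0.20 × 80 = 16 umol/L from a baseline of 80, but 0.20 × 300 = 60 umol/L from a baseline of 300. The raw change treats these as very different events.

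What is at stake is how precisely the trial can describe kidney function in the two arms. Section 2 makes kidney injury a safety objective, and section 10.4 names insufficient fluid as a possible result of wrong guidance. A Mann-Whitney p-value alone also gives no estimate or interval for the size of renal harm that the data exclude.

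**Working it through.** **1. The plan's own figure.** Section 4.4 states that "170 participants (85 per group) are needed to achieve 80% power". It takes this from a "mean difference of 1.37 L in positive fluid balance at 72 hours between groups", with SDs of 2.85 and 3.44. The standard error is √((2.85² + 3.44²)/85) = √(19.956/85) = 0.4845. The noncentrality is 1.37/0.4845 = 2.83, and Welch power is 80.3%. The figure reproduces. It concerns fluid volume only. The protocol gives no SD, effect, correlation or power target for creatinine, so every creatinine input below is an assumption.

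**2. Adjustment alone, in closed form.** Let ρ be the baseline-to-follow-up correlation, with equal SDs:

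- variance of a change score: 2·SD²·(1 − ρ)
- residual variance after ANCOVA: SD²·(1 − ρ²)
- ratio, ANCOVA to change: (1 + ρ)/2

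If ANCOVA has 80% power at two-sided 0.05, the change score has power Φ(2.802·√((1 + ρ)/2) − 1.960). At ρ = 0.5 this is Φ(2.426 − 1.960) = 67.9%. At ρ = 0.7 it is Φ(2.583 − 1.960) = 73.3%. Over ρ = 0.3 to 0.9 the loss runs from about 18 points down to 2.

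The result depends on the equal-SD assumption. For ρ from 0.5 to 0.8, a follow-up SD 1.3 times the baseline SD cuts the loss to about 4 to 0 points. A follow-up SD 0.7 times the baseline SD raises it to about 30 to 32 points.

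**3. Adjustment plus log scale, by simulation.** The formula covers normal data and not a rank test, so the tests were also simulated. Assumptions: 85 per arm, lognormal creatinine, log-SD 0.5, a true uniform 15% rise in one arm, 2,000 replicates.

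| ρ | t on raw change | Mann-Whitney on raw change | log ANCOVA | gain over t | gain over Mann-Whitney |
|---|---|---|---|---|---|
| 0.6 | 47% | 50% | 61% | 14 | 11 |
| 0.7 | 59% | 62% | 71% | 12 | 9 |
| 0.8 | 74% | 79% | 85% | 11 | 6 |

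One power estimate near 50% has a simulation error of √(0.25/2,000), about 1.1 points. A separate run over ρ = 0.5, 0.6, 0.7, 0.8 and 0.9 gave gains over Mann-Whitney of about 12, 10, 10, 7 and 2 points. Gains over the t-test ran from about 14 down to about 3. The small gain at 0.9 is partly a ceiling, because every test there exceeds 95%. With a 10% rise instead, the gap to Mann-Whitney at 0.9 is about 6 points.

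**4. Type I error.** With no true difference, rejection rates were 4.6% to 5.4% for the tests compared.

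**5. A different harm pattern.** Suppose creatinine doubles in 20% of one arm and is unaffected in the rest. At ρ = 0.6, 0.8 and 0.9:

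- t on raw change: 57%, 77%, 92%
- log ANCOVA: 52%, 71%, 89%
- Mann-Whitney: 40%, 50%, 59%

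Here log ANCOVA trails the raw-change t-test by 5, 6 and 3 points, but leads Mann-Whitney by 12, 21 and 30. Baseline-adjusted raw creatinine matches or beats the raw-change t-test. The loss under concentrated harm therefore comes from the log scale and not from the adjustment.

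**The case against.** The strongest reply is that nothing here is invalid. The planned tests hold their level, the trial is powered only for fluid volume, and creatinine change is two of six renal items. The objective in section 2 is worded as the rate of acute kidney injury, which the KDIGO endpoints address directly. All of that stands, and it limits this to an optional gain in precision.

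Three stronger readings are tempting, and the documents support none of them.

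- A reader might infer one definite power loss, for example around 10 to 15 points. The protocol supplies none of the inputs, and plausible choices move the figure from almost nothing to 30 points or more.
- A reader might infer that a few high-baseline patients will dominate the comparison. That can happen with a t-test. If the changes are judged non-normal, section 9.2 moves to Mann-Whitney, and a rank test is not driven by a few extreme values.
- A reader might infer that kidney harm in an arm given less fluid would be missed. Less fluid in the guided arm is the direction seen in the reference study and not something the protocol fixes. The binary renal endpoints would still be reported.

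It could also be said that the choice belongs to a separate analysis plan. That does not hold here, because section 9.2 names the tests for continuous endpoints and postpones only the binary and time-to-event ones.

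**Conclusion.** The point holds as a minor one. The protocol fixes an unadjusted two-sample test for two change-from-baseline endpoints whose baseline it already collects. This loses precision without biasing the comparison or inflating Type I error.

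Under the stated assumptions (85 per arm, log-SD 0.5, uniform 15% rise, ρ from 0.9 down to 0.5), log ANCOVA gains about 2 to 12 points over Mann-Whitney and about 3 to 14 over the t-test. Under concentrated harm the log scale gives up about 2 to 7 points to the raw-change t-test, while still beating Mann-Whitney by about 11 to 30. The case for baseline adjustment survives both patterns. The case for the log scale depends on which pattern is expected.

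**What to change.** In section 9.2, state that creatinine at 48 h, and at day 7 or discharge, is compared by ANCOVA with triage creatinine as covariate. Use the log scale for both and report the between-arm ratio with its 95% confidence interval. Keep the change in creatinine level, as defined in section 8.1.2, as a reported supportive result, and say in 8.1.2 which of the two is the main estimate.

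No new measurements are needed. The cost is that the main estimate becomes a ratio instead of a umol/L difference, and that it is somewhat less sensitive to harm confined to a few patients. The KDIGO endpoints also cover that pattern, and the retained change in level keeps it visible.
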